## Statistical Design and Methods

The primary endpoint of the trial is the tolerability rate, which is calculated as the percentage of patients for which no CTC Grade 4 toxicity occurs during the radiation therapy and until 6 weeks after its termination. The target tolerability rate is 90%, and a tolerability rate of less or equal to 70% is considered to be not of interest. Denoting the tolerance rate by *p*, the related test problem can be formulated as *H*_*0*_: *p *≤ *p*_*0 *_= 0.70 versus *H*_1_: *p *≥ *p*_1 _= 0.90 which will be assessed at one-side significance level *α *= 0.05.

The trial is designed as a two-stage study with a planned interim analysis, allowing for early stopping, and a power of 0.90 to reject the null hypothesis. In the first stage, 15 patients are enrolled. If all these patients would tolerate radiation therapy according to the definition of the primary endpoint, the study would stop with rejection of the null hypothesis. The study would terminate with acceptance of the null hypothesis, if less than 12 of the first 15 patients would tolerate the radiation therapy. According to the current design, the trial would continue with the second stage enrolling further 22 patients, if the number of patients that tolerate radiation therapy is between 12 and 14. In the final analysis, the null hypothesis can be rejected if the product of the one-sided p-values of the two stages is lower or equal to 0.021. With an expected sample size of 21.4 for a tolerability rate of *p*_0 _= 0.70 (i.e., under the null hypothesis), this design shows similar characteristics as Simon's (1989) optimal design whose expected sample size is 21.2. under the same scenario [34]. However, the adaptive two-stage design implemented in this trial allows a data-driven modification of the sample size of the second stage based on the results of the interim analysis or on external information while the specified significance level is controlled when the decision rules defined above are adhered to [35].

Additionally to the hypothesis testing approach, the primary endpoint will be analysed by applying Bayesian methods. Starting with the uniform distribution for the tolerability rate as prior distribution for the preceding trial OVAR-IMRT-01 [26,30,31], the posterior distribution of this trial is derived which serves as prior distribution for the current study OVAR-IMRT-02. Employing the results of OVAR-IMRT-02 leads to an updated posterior distribution for the tolerability rate from which Bayesian inference on *p *will be derived.

The secondary outcome variables will be evaluated by application of methods of descriptive data analysis. Appropriate measures of the empirical distribution as well as 95% confidence intervals will be calculated. All statistical analyses will be performed with SAS version 9.0 or higher.

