### Ethics, informed consent and safety

The final protocol was approved by the ethics committee of the University of Heidelberg, Heidelberg, Germany (Nr: S-353/2008). Additionally, a positive vote of the Bundesamt für Strahlenschutz (BfS) has been obtained. This study complies with the Helsinki Declaration in its recent German version. The trial will also be carried out in keeping with local legal and regulatory requirements. The ClinicalTrials.gov Protocol ID is NCT01180504.

All severe adverse events have to be reported immediately to the principal investigator. In addition, side effects and patient safety will be monitored by an independent data safety monitoring committee (DMC), composed of one radio oncologist, one gynaecologist and one statistician. In case of frequent or particularly serious adverse events, then the DMC would have to consider termination of the study. This evaluation has to be made in consideration of risk/benefit. The DMC will meet on a regular basis.

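### Stage 1 futility is tied to one look after 15 patients; adding a stop at the fourth grade 4 failure, when acceptance of H0 is already fixed, would be a cheap improvement

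*Protocol article*

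**What the plan says.** Under Statistical Design and Methods, the primary endpoint is the "percentage of patients for which no CTC Grade 4 toxicity occurs during the radiation therapy and until 6 weeks after its termination". The uninteresting rate is p0 = 0.70 and the target is p1 = 0.90, with one-sided alpha 0.05 and "a power of 0.90 to reject the null hypothesis".

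The design has two stages with one planned interim analysis. "In the first stage, 15 patients are enrolled". The trial then takes one of three paths:

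- it rejects H0 if all 15 tolerate treatment;
- it accepts H0 "if less than 12 of the first 15 patients would tolerate the radiation therapy";
- it enrols 22 more after 12 to 14 successes, and rejects at the end if the product of the two stage-wise p-values is at most 0.021.

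The second-stage size may be changed at the interim. The stated expected sample size at p0 is 21.4, against 21.2 for Simon's optimal design.

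Under Ethics, informed consent and safety, severe adverse events go to the principal investigator at once and an independent committee meets regularly. "In case of frequent or particularly serious adverse events, then the DMC would have to consider termination of the study". No count is attached to this.

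**The concern.** A failure here is a grade 4 toxicity, and once recorded it cannot be reversed. Futility in stage 1 is the same event as a fourth failure among the first 15 patients, so from that moment no later result can lead to rejection. The article names no stop at that point. Its decision rule is linked to the interim analysis, and the safety text leaves an earlier stop to the committee's judgement.

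At stake is exposure. The endpoint is severe toxicity of whole-abdominal irradiation, and anyone enrolled after the fourth failure takes that risk when the primary hypothesis is already settled. The same happens in stage 2 once too many failures have accrued for the p-value product to reach 0.021.

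**Working it through.** **Inputs.** From Statistical Design and Methods: n1 = 15, n2 = 22, p0 = 0.70, p1 = 0.90, futility at 11 or fewer successes, efficacy at 15, product criterion 0.021. Radiotherapy lasts 4 weeks (Duration of treatment), and recruitment is planned over 36 months (Duration of the study).

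**1. The plan's own figures.** With X1 ~ Bin(15, 0.70), P(X1 = 12, 13, 14) = 0.1700, 0.0916, 0.0305, which sum to 0.2921.

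E[N] = 15 + 22 × 0.2921 = 21.43, the stated 21.4. The formula charges 15 patients to every trial that fails at stage 1, so the published figure describes a completed first stage.

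A grid search for Simon's optimal design gives 21.23, the stated 21.2.

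**2. Stage 2 critical values.** These are the smallest counts out of 22 for which the product of the p-values is at most 0.021. Rejection becomes impossible at failure number 22 − (successes needed) + 1.

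| Stage 1 successes | Stage 1 p-value | Successes needed of 22 | Product at that count | Product one count lower | Rejection impossible at stage 2 failure |
|---|---|---|---|---|---|
| 12 | 0.2969 | 19 | 0.0202 | 0.0488 | 4th |
| 13 | 0.1268 | 18 | 0.0209 | 0.0397 | 5th |
| 14 | 0.0353 | 16 | 0.0174 | 0.0237 | 7th |

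**3. Type I error and power.** At p = 0.70: 0.0047 + 0.1700 × 0.0681 + 0.0916 × 0.1645 + 0.0305 × 0.4942 = 0.0465. The same sum at p = 0.90 gives 0.904. Curtailment removes only paths that already end in acceptance of H0, so both figures stay the same.

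**4. Curtailing stage 1.** Let T be the patient number of the fourth failure: P(T = t) = C(t − 1, 3)(1 − p)^4 p^(t − 4). Futility is the event T ≤ 15. With a lag of L patients already started, the saving is max(0, 15 − T − L).

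| | p = 0.60 | p = 0.70 | p = 0.90 |
|---|---|---|---|
| P(stage 1 futility) | 0.909 | 0.703 | 0.056 |
| Mean T given futility | 9.2 | 10.4 | 12.2 |
| Spared given futility, L = 0 | 5.8 | 4.6 | 2.8 |
| Spared given futility, L = 1 | 4.9 | 3.7 | 2.0 |
| Spared given futility, L = 3 | 3.1 | 2.1 | 0.9 |
| E[N], as planned | 17.0 | 21.4 | 31.2 |
| E[N], stage 1 curtailed, L = 0 | 11.7 | 18.2 | 31.1 |

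At p = 0.70 the step is 0.703 × 4.57 = 3.21, and 21.43 − 3.21 = 18.2. Given futility there, the fourth failure falls before patient 15 with probability 0.917.

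**5. Both stages.** Applying the stage 2 limits as well gives E[N] = 16.05 at p = 0.70 with no lag. With L = 1 to 3, E[N] is 18.9 to 19.9 (stage 1 only) or 16.9 to 18.5 (both stages).

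**6. Why L = 1 to 3.** Uniform accrual is an assumption: 37/36 = 1.03 patients a month. Four weeks of treatment plus the 6-week window is 10 weeks, or about 2.4 patients. A success needs the full window, but a failure is known when it occurs, so the lag could be shorter.

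**The case against.** A single look after stage 1 is the usual two-stage form, the boundary is sound, and every stated operating characteristic reproduces. Nothing needs correcting as an error. That stands.

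A reader might infer that the plan requires patients to go on being treated after the trial has failed, or forbids acting before patient 15. The text says neither. Once a fourth failure is known, the stated condition is certain to be met, and stopping then is compatible with the wording. Weekly evaluation, twice-weekly blood counts, immediate reporting and an independent committee that includes a statistician also watch the very events that decide futility. So a mid-stage stop is possible. It is, however, discretionary and not linked to the endpoint count, and the published 21.4 does not reflect it.

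The article condenses a full protocol that is not shown, and operational stopping detail may be there. That limits the point to a recommendation on the rule as published.

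A reader might also put the saving at 5 to 7 patients. That assumes no lag, and the upper end (7.2) needs p = 0.50, well below p0.

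**Conclusion.** The point holds as a cheap improvement. The futility rule is linked to one look after 15 patients although the fourth failure already decides it, and no trigger based on that count is stated, so enrolment may continue after rejection has become impossible.

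The benefit is moderate where the treatment is poorly tolerated: 2.1 to 4.6 patients spared given stage 1 futility at p = 0.70, depending on how many have already started. At the target rate it is negligible. These sizes rest on independent outcomes with a constant rate and on the assumed lag; the unchanged type I error and power do not depend on the lag. The stage 2 limits hold only for n2 = 22.

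**What to change.** Add to Statistical Design and Methods: *Enrolment stops with acceptance of H0 as soon as rejection is no longer possible. In stage 1 this is the fourth primary-endpoint failure among the first 15 patients. In stage 2 with 22 patients it is the 4th, 5th or 7th stage 2 failure after 12, 13 or 14 stage 1 successes. If the stage 2 size is changed at the interim, these limits are recomputed from the p-value product criterion before stage 2 starts.* The rule concerns enrolment only; it says nothing about the care of patients already in treatment.

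If it is adopted, report the expected sample size with and without curtailment, so that the 21.4 remains comparable with Simon's 21.2.

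The cost is a running count of endpoint failures, which the existing reporting route can supply, and fewer patients for the secondary and Bayesian analyses, but only in a trial that has already failed on its primary test.

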### Investigation schedule

#### Therapy Indication

For each patient, the oncologic treatment concept after diagnosis is based on a tumor board review, following approved standard therapies and current guidelines. Consent of the colleagues from gynaecology, internal medicine and radiation oncology are obligatory.

#### Pre-therapeutic examinations

A complete staging is performed before surgery and/or chemotherapy, including abdominopelvic CT scan or MRI, radiography or CT scan of the chest, liver sonography, pelvic examination, transvaginal sonography, CA-125. After completion of chemotherapy, the complete remission is assessed by pelvic examination, transvaginal sonography and measure of CA-125.

The baseline visit is performed at study enrollment, after obtaining of the written consent of the patient. It includes blood test, clinical examination and quality of life questionnaire (EORTC-QLQ30).

#### Radiotherapy-planning

After immobilisation in a vacuum mattress and a scotch cast head mask (arms above the head) the patients undergo a native and contrast enhanced abdomino-pelvic computed tomography (optionally with 4D respiratory triggering). This CT scan is used for the restaging and for the radiation planning.

The clinical target volume (CTV) includes the whole peritoneal cavity extending from diaphragm to douglas cavity, the liver surface, and the pelvic and para-aortic node regions. The planning target volume (PTV) encompasses an axial margin of 1.5 cm around the CTV (2.5 cm in the cranial direction). Organs at risk are kidneys, liver (except the 1 cm-outer border), lungs, bones (vertebral bodies and pelvic bones), hear and spinal cord.

A dose of 30.0 Gy is prescribed to the median of the PTV. Inverse radiation planning is performed according to the national DIN norm and international recommendations (ICRU 50 Report 1999). The goal of optimization is to deliver a dose distribution in the PTV as homogeneous as possible in spite of maximal sparing of OARs with a high priority on liver, kidney and bone marrow. Tolerated maximum doses to OARs are not to exceed the TD5/5 for each organ (31).

#### Radiation therapy

Irradiation is applied as helical intensity-modulated radiation therapy (IMRT) using a tomotherapy device (Madison, Wisconsin, USA) with 6 MeV photons. Control of positioning accuracy is performed daily with the integrated megavoltage computed tomography for tomotherapy (MV-CT scan, 3.5 MV).

#### Duration of treatment

The delay between the last chemotherapy and the onset of radiation should not exceed 10 weeks. The duration of the treatment planning is estimated about 2 or 3 weeks. The duration of radiotherapy is 4 weeks (20 fractions). The overall daily treatment time is expected to be about 15 to 20 minutes with a mean daily "time on table" of about half an hour.

#### Treatment schedule

The radiotherapy is performed on an out-patient basis with the possibility of hospital admission if required.

#### Monitoring during treatment

Patients are evaluated weekly during radiotherapy. Antiemetic and antidiarrheal medications are prescribed as required. Blood count is assessed twice weekly. Toxicities are graded according to the National Cancer Institute Common Toxicity Criteria version 3.0. The quality of life is assessed at the last treatment fraction using EORTC-QLQ30 questionnaire. The documentation of acute hematologic, genito-urinary and gastro-intestinal acute toxicities is especially relevant.

### Follow up

Follow-up visits are scheduled in addition to the standard gynaecology follow-up program at 6 weeks, 3, 6, 9, 12, 15, 18, 24, 30 and 36 months, respectively, after completion of radiotherapy. Each visit includes blood test, CA-125, pelvic examination, transvaginal ultrasound, recording of adverse events and assessment of quality of life (questionnaire EORTC-QLQ30). The documentation of late genito-urinary and gastro-intestinal toxicities (such as bowel obstruction) is especially relevant. Additionally, a contrast-enhanced abdomino-pelvic CT scan or MRI will be performed at 6, 12 und 24 months, respectively.

### Duration of the study

The primary objective of the study is to prove the good treatment tolerance, defined as non-occurrence of CTC grade 4 toxicities during radiotherapy and till 6 weeks after its completion. To assess the primary endpoint, the final study visit will be 6 weeks after the last patient completed the radiotherapy. The study ends three years after the last patient was treated. Recruitment of the patients is planned over a time period of 36 months; follow-up duration will be 36 months.

### Data Handling, Storage and Archiving of Date

All findings including clinical and laboratory data will be documented by the investigator or an authorized member of the study team in the subject's medical record and in the CRF. The data will be stored and archived according to the §13 of the German GCP-Regulation and §28 c of the German X-Ray Regulation (StrlSchV) for at least 30 years after the trial termination.

### Ethics, informed consent and safety

The final protocol was approved by the ethics committee of the University of Heidelberg, Heidelberg, Germany (Nr: S-353/2008). Additionally, a positive vote of the Bundesamt für Strahlenschutz (BfS) has been obtained. This study complies with the Helsinki Declaration in its recent German version. The trial will also be carried out in keeping with local legal and regulatory requirements. The ClinicalTrials.gov Protocol ID is NCT01180504.

All severe adverse events have to be reported immediately to the principal investigator. In addition, side effects and patient safety will be monitored by an independent data safety monitoring committee (DMC), composed of one radio oncologist, one gynaecologist and one statistician. In case of frequent or particularly serious adverse events, then the DMC would have to consider termination of the study. This evaluation has to be made in consideration of risk/benefit. The DMC will meet on a regular basis.

In the previous phase-I study, small bowel obstruction due to adhesions occurred in 3 of 10 patients, 2.5, 3 and 13 months respectively after radiotherapy. The exact role played by radiotherapy in the development of peritoneal adhesions remains unclear and further studies are needed to evaluate this problem. Risk factors for late bowel toxicity are suggested by literature: dose escalation with a total abdominal dose over 30 Gy, pelvic-boost and/or para-aortic boost and previous second-look laparotomy are associated with a significant increase in small bowel obstruction [23,32,33]. Given that the addition of pelvic boost treatment is not clearly beneficial in the literature; the routine use of a pelvic boost in consolidation WAR should be questioned [23]. With respect to these arguments, this study was designed with careful attention to keeping the risk for late bowel toxicity as low as possible and bowel adverse events will be monitored accurately.

Intensity-modulated WAR could offer a new therapeutic option for consolidation treatment of advanced ovarian carcinoma after adjuvant chemotherapy in selected subgroups of patients. However, further consequent studies are needed to draw firm conclusions regarding the value of consolidation radiotherapy in the multimodal treatment of ovarian carcinoma, including immunologic and biologic therapies in the future.

## Abbreviations

CRF: Case Report Form; CTCAE: Common Terminology Criteria for Adverse Events; CTV: Clinical Target Volume; DMC: Data Monitoring Committee; FIGO: International Federation of Gynaecology and Obstetrics; GCP: Good Clinical Practice; IMRT: Intensity Modulated Radiation Therapy; PTV: Planning Target Volume; TD5/5: Tolerance Dose 5% over 5 years; WAR: Whole-Abdominal Radiotherapy
